### 2.3. Eligibility Criteria

#### 2.3.1. Inclusion Criteria

Signed informed consent;Age between 18 and 65 years;Newly diagnosed OSA according to the American Academy of Sleep Medicine Guidelines (overnight PSG with an apnea-hypopnea index (AHI) ≥ 5 events per hour, hypopneas defined by ≥10 s of airflow reduction accompanied by ≥3% desaturation or an arousal) [21];Ability to complete all relevant tests and follow-up visits.

#### 2.3.2. Exclusion Criteria

History of any chronic disease other than overweight and obesity;Severe psychiatric condition that could affect cognitive functions;Chronic use of medication or nicotine that may affect the study results;Prior neuropsychological assessment performed less than 6 months before study enrollment;Prior therapy for OSA (e.g., PAP, upper airway surgery, oral appliance);Motor or sensory deficits that would significantly complicate test administration;Patients with insufficient Slovak language proficiency for valid participation in the study;Considered by the study team as not suitable for enrollment based on clinical judgment.

#### 2.3.3. Withdrawal Criteria

If a patient with a stable medical condition at enrollment experiences a deterioration of the existing condition or develops a new condition, the participant will be assessed by the study physician, and the treating physician(s) will be consulted. If either the study physician or the treating physician considers continued participation inadvisable, the participant will be immediately withdrawn from the study and referred back to their treating physician for appropriate management. Given the observational nature of the study and the use of standard-of-care procedures, no study-specific risks or harms are anticipated.

### 2.4. Baseline Measures, Exposures and Confounders

#### 2.4.1. Polysomnography

PSG (using the Alice 6 Philips-Respironics device, Murrysville, PA, USA) represents a laboratory examination simultaneously recording vital functions such as sleep/wakefulness, breathing, blood oxygen saturation, heart activity, limb movements, etc. It will be performed on all patients who are hospitalized in the Sleep Laboratory of the 1st Department of Neurology with suspicion of OSA to confirm or exclude this diagnosis, and in patients with confirmed OSA, to characterize the severity and specific features of the disorder. The sleep examination will include a questionnaire-based assessment of daytime sleepiness (Epworth Sleepiness Scale) and sleep quality (Pittsburgh Sleep Quality Index).

#### 2.4.2. Neuropsychological Assessment

The cognitive evaluation will focus on core cognitive domains and will include tests from the NEUROPSY battery adapted for the Slovak population: (1) Rey auditory—verbal learning test, (2) Controlled oral word association test, (3) Category fluency test, (4) Trail-making test, (5) Stroop color and word test, (6) Digit span and from short Czech neuropsychological battery, (7) Figure copy task. Based on the results, the presence of cognitive dysfunction will be determined. Further questionnaire-based assessments will be conducted, including the Generalized anxiety disorder 7-item scale (GAD-7), Patient health questionnaire-9 (PHQ-9), and screening of cognitive functions through the Montreal cognitive assessment (MoCA). The MoCA will be included as a brief screening tool to allow external comparability with other studies but will not substitute for the comprehensive battery.

*A detailed description of each cognitive test and questionnaire is provided in Appendix A (Table A1). All participants complete the tests in a standardized order as listed.*

#### 2.4.3. Brain Magnetic Resonance Imaging and Volumetry

MRI of the brain will be performed using a PHILIPS Ingenia 3T Omega HP scanner (Philips Healthcare, Best, The Netherlands). Standard sequences will include T1- and T2-weighted imaging, FLAIR sequences in axial, coronal, and sagittal planes, diffusion-weighted imaging (DWI), apparent diffusion coefficient (ADC), and susceptibility-weighted imaging (SWI). Brain volumetric analysis will be performed using the icobrain software (version 5.16.6; icometrix NV, Leuven, Belgium), enabling quantitative assessment of total and regional brain volumes, including total brain volume, gray and white matter volumes, hippocampal volume, cortical thickness, and other selected regional structures relevant to cognitive function (units: mL or mm^3^; volume changes reflect structural brain alterations).

#### 2.4.4. Anthropometric Measurements

Anthropometric assessment will focus on the evaluation of overweight and obesity. Body mass index (BMI) will be calculated as weight in kilograms divided by height in meters squared. Body composition will be assessed using bioelectrical impedance analysis (BIA) with Omron and InBody devices. A comprehensive analysis of body composition, including fat mass, fat-free mass, and body fat percentage, will be performed using the InBody 720 device (Biospace, Seoul, Republic of Korea), which utilizes direct segmental multi-frequency BIA. In addition, body fat estimation will be obtained using skinfold thickness measurements with calipers. Daily physical activity will be assessed using the Slovak version of the Lagerros questionnaire.

#### 2.4.5. Blood and Saliva Sampling

Venous blood and saliva samples will be collected for laboratory analyses. In blood, we will assess lipid and glucose metabolism, inflammatory, neuronal, and metabolic markers, metalloproteinase activity, and hypoxia-related gene expression in peripheral blood mononuclear cells (PBMCs). Oxidative stress and selected metabolic and lipid markers will be analyzed in both blood and saliva.

The examination of the lipoprotein profile will involve determining the levels of total cholesterol, low density lipoprotein (LDL) cholesterol, high density lipoprotein (HDL) cholesterol, and triglycerides in a certified laboratory using an autoanalyzer (Siemens Healthcare Diagnostics Inc., Tarrytown, NY, USA) following standard procedures with enzymatic kits (Roche Diagnostics, Lewes, UK). Detailed lipid metabolism with a focus on the determination of HDL and LDL subfractions of lipoproteins in plasma will be analyzed using electrophoresis on a polyacrylamide gel system called Lipoprint (Quantimetrix Corporation, Redondo Beach, CA, USA).

The role of oxidative stress will be analyzed by monitoring plasma and saliva antioxidant capacity (spectrophotometrically) and levels of markers of oxidative damage to lipids (lipoperoxides) (spectrophotometrically). All markers will be determined in both plasma and unstimulated whole saliva.

The role of endothelial function, metabolic regulation, and systemic inflammation will be assessed by measuring plasma levels of asymmetric dimethylarginine (ADMA), adiponectin, and lipopolysaccharide-binding protein (LBP), respectively. ADMA serves as an endogenous inhibitor of nitric oxide synthase and reflects endothelial dysfunction. Adiponectin is a key adipokine involved in glucose and lipid metabolism with anti-inflammatory properties, and LBP is a marker of bacterial endotoxin exposure and immune system activation. All markers will be quantified using validated immunoassays according to the manufacturers’ protocols.

PBMCs will be isolated from 15–20 mL of blood using Ficoll Paque Plus gradient centrifugation and stored at −80 °C in CryoStor medium (BioLife Solutions, Inc., Bothell, WA, USA) until nucleic acid extraction. Plasma will be collected from each sample for zymographic determination of matrix metalloproteinase activity. PBMCs will be used to monitor mRNA expression of selected genes using reverse transcription quantitative polymerase chain reaction (RT-qPCR) with TaqMan probes (Thermo Fisher Scientific Inc., Waltham, MA, USA). Relative gene expression will be calculated from CT values using Bio-Rad CFX Manager software (version 3.1; Bio-Rad Laboratories, Hercules, CA, USA).

ApoE genotyping will be performed to investigate genetic predisposition to neurodegenerative and vascular changes.

#### 2.4.6. Gut Microbiome from Stool

Stool samples will be collected in sterile tubes for cultivation and in DNA/RNA Shield tubes (Zymo Research, Irvine, CA, USA) for nucleic acid preservation. Gut microbiome characterization will be performed using up-to-date methods, including 16S rRNA V3–V4 region metagenomic sequencing on the Illumina MiSeq system with commercially available library and sequencing kits (BiovendorMDx (BioVendor—Laboratorní medicína a.s., Brno, Czech Republic); MiSeq^®^ Reagent Kit v3 (Illumina, Inc., San Diego, CA, USA)). Sequencing data will be processed using established bioinformatics pipelines, including quality filtering, read assembly, and taxonomic assignment. Downstream analyses will include assessment of microbial composition as well as alpha and beta diversity metrics. In vitro cultivation of gut microbiota will be performed to complement sequencing-based analysis, enabling quantitative and functional assessment of viable bacterial populations. The combination of cultivation and flow cytometry will allow high-resolution identification and quantification of bacterial species within complex communities. Additionally, culture-based analyses will provide insight into microbial functional outputs, including the production of extracellular vesicles and extracellular RNA, such as miRNA.

#### 2.4.7. Vascular Functions

Subclinical atherogenesis will be examined using peripheral arterial tonometry (PAT) with the EndoPAT device (Itamar Medical Ltd., Caesarea, Israel). The examination is performed non-invasively with sensors placed on the second finger of both hands. One limb is used to determine resting arterial tonometry, while occlusion of blood flow in the brachial artery with a cuff pressure monitor is induced on the other limb, followed by the observation of reactive hyperemia. The reactive hyperemia index (RHI), a parameter of endothelial function, and the augmentation index (AI), a parameter of arterial stiffness, will be determined.

#### 2.4.8. Baroreflex Sensitivity

The function of the autonomic nervous system (baroreflex sensitivity) will be measured using a non-invasive system, the Finometer^®^ PRO (Finapres Medical Systems B.V., Enschede, The Netherlands), which continuously records blood pressure and pulse frequency values on the fingers of the hand. Autonomic reactivity will be evaluated from spontaneous blood pressure fluctuations.

### 2.5. Outcome Measures

#### 2.5.1. Primary Outcome Measures

##### Cognitive Function

The primary outcome of the study is cognitive function assessed by a comprehensive neuropsychological battery. Primary cognitive outcomes will be derived from test performance across the main cognitive domains including memory, executive functions, attention, language, and visuoconstructional abilities. Cognitive performance will be evaluated both cross-sectionally at baseline, to characterize the prevalence, severity, and pattern of cognitive deficits in patients with OSA, and longitudinally as change in cognitive performance from baseline to 12 months. PAP therapy adherence will be treated as an exposure variable in analyses of longitudinal cognitive change.

To improve comparability across tests and reduce measurement variability, standardized z-scores will be calculated for each neuropsychological measure and subsequently aggregated into domain-specific composite scores. In addition to statistical significance, cognitive outcomes will also be evaluated for clinical relevance. Clinically meaningful improvement will be defined as a change greater than 1 standard deviation (SD) from baseline in domain-specific scores or a shift from impaired to normative performance range (e.g., from ≤5th percentile to >15th percentile) [22]. This ensures that changes in test performance reflect not only statistical but also functional significance.

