#### 2.5.2. Secondary Outcome Measures

##### Changes in Baseline Measures

After 12 months of PAP treatment, patients will undergo the same assessments as during their initial hospitalization (besides ApoE genotyping), following the original protocol. This will include overnight PSG, neuropsychological testing, brain imaging, brain volumetry, anthropometric measurements, blood and saliva samples, gut microbiome, vascular functions and baroreflex sensitivity assessments. All collected data will be compared with baseline values, allowing us to explore the associations between PAP therapy and changes in cognitive and other selected parameters. All secondary analyses are considered exploratory and hypothesis-generating.

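### The rule for clinically meaningful improvement makes no allowance for retest error, practice or regression to the mean, so it cannot ensure that a change is functionally significant

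*Protocol article*

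**What the plan says.** Section 2.5.1 of the protocol article names five domains: "memory, executive functions, attention, language, and visuoconstructional abilities". Within these, "standardized z-scores will be calculated for each neuropsychological measure and subsequently aggregated into domain-specific composite scores". The rule has two limbs joined by *or*: clinically meaningful improvement is "a change greater than 1 standard deviation (SD) from baseline in domain-specific scores or a shift from impaired to normative performance range". The second limb, the move from the impaired to the normative range, is illustrated as "e.g., from ≤5th percentile to >15th percentile". The section then concludes: "This ensures that changes in test performance reflect not only statistical but also functional significance".

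Section 2.5.2 says that at 12 months "patients will undergo the same assessments as during their initial hospitalization (besides ApoE genotyping), following the original protocol". The Discussion concedes that there is no placebo or untreated control group. Section 2.7 analyses cognitive change with a linear mixed-effects model containing a time-by-adherence interaction; the improvement rule does not enter that model.

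**The concern.** A participant whose cognition has not changed can still score higher at 12 months for three reasons: measurement error at both visits, familiarity with the tests, and, for those who scored low at baseline, regression to the mean. The rule compares the raw change, or a change of category, with fixed cut-offs and allows for none of the three. Its second limb applies only to participants selected for a low baseline score, where regression to the mean is strongest. Without an untreated group, nothing else in the rule separates these artefacts from real gain.

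What is at stake is the clinical-relevance statement attached to the primary outcome. An improved proportion would be read as functional benefit when part of it, possibly a large part among the baseline-impaired, would arise with no change at all.

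**Working it through.** **The plan's own figures.** The article gives no false-improvement rate to reproduce. Its sample size does reproduce. A two-sided paired t-test with d = 0.5, α = 0.05 and 80% power needs 34 (power 0.808), and 34/0.85 = 40. Four predictors with f² = 0.15 need 85 (power 0.803), and 85/0.85 = 100. Neither figure uses the improvement rule.

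**Inputs from Section 2.5.1.** Limb 1: change above 1 SD. Limb 2, with the illustrative percentiles: baseline z ≤ −1.645 and follow-up z > −1.036. The smallest change that satisfies limb 2 is just over −1.036 + 1.645 = 0.61 SD.

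**Assumptions, not in the article.** No true change; baseline and 12-month domain scores bivariate normal with SD 1; cohort at the normative mean; retest correlation r from 0.6 to 0.9; mean practice gain p of 0 or 0.25 SD.

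**Limb 1 alone.** The change has mean p and SD √(2(1−r)), so the false-improvement rate is 1 − Φ((1−p)/√(2(1−r))). For r = 0.7 and p = 0: SD = √0.6 = 0.775, 1/0.775 = 1.291, rate 9.8%. For p = 0.25: 0.75/0.775 = 0.968, rate 16.6%.

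**Regression to the mean.** Participants at or below the 5th percentile have mean baseline z = −φ(1.645)/0.05 = −0.1031/0.05 = −2.06. With r = 0.7 their expected follow-up is 0.7 × (−2.06) = −1.44, a gain of 0.62 SD with no true change.

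**Either limb, no true change** (numerical integration, agreeing with simulation):

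| | r = 0.6 | r = 0.7 | r = 0.8 | r = 0.9 |
|---|---|---|---|---|
| Per domain, all participants, p = 0 | 13.5% | 10.2% | 6.0% | 1.4% |
| Per domain, all participants, p = 0.25 | 20.4% | 17.0% | 12.2% | 5.0% |
| At or below 5th percentile at baseline, p = 0 | 48% | 36% | 22% | 7% |
| At or below 5th percentile at baseline, p = 0.25 | 60% | 50% | 37% | 18% |

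With 100 × 0.85 = 85 completers, the first row is about 11, 9, 5 and 1 false improvers per domain, and the second about 17, 14, 10 and 4.

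**Contribution of limb 2.** Across the whole cohort it adds only 0.2 to 0.5 percentage points per domain, because few participants are impaired at baseline. Within the impaired group it matters more: at r = 0.7 and p = 0 it raises the rate from 30% to 36%, and at r = 0.9 from 3.5% to 7%.

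**Effect of averaging tests.** Take three tests, each with retest correlation 0.7, inter-test correlation 0.5 and independent errors (all assumed). The composite variance is (1 + 2 × 0.5)/3 = 0.667, so its SD is 0.82. The error variance is 0.3/3 = 0.1, so the composite retest correlation is 1 − 0.1/0.667 = 0.85. With p = 0 the rule is met by 1.4% if the composite is left at SD 0.82, or 3.6% if it is restandardised to SD 1; among the impaired, 11% or 15%. Left at SD 0.82, a −1.645 cut-off flags Φ(−1.645/0.816) = 2.2% of the reference population rather than 5%.

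**The case against.** The strongest reply is that the article does address measurement error: "To improve comparability across tests and reduce measurement variability, standardized z-scores will be calculated for each neuropsychological measure", followed by aggregation. That stands in part. The three-test example shows that averaging can bring the cohort-wide rate down to a few per cent. But averaging does not remove practice or regression to the mean, and a domain measured by a single test gets no such benefit.

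The rule is also only an addition to the statistical analysis. That stands in full: the mixed model and the sample size do not depend on it, and the Discussion says that causal inference will be limited.

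A reader might go further and infer any of the following, none of which the article supports:
- *That the rule will mislabel many participants.* This needs a retest correlation and a practice gain that the article does not state; at r = 0.9 without practice the rate is 1.4%.
- *That around 40% would be called improved in at least one domain.* At r = 0.7 without practice and with independent errors, five domains do give 41%, but the article states no any-domain rule.
- *That the unequal limbs drive the problem.* The 0.61 SD figure rests on percentiles given as an example, and two alternative criteria joined by *or* do not contradict each other.
- *That the improved proportion would be credited to PAP.* The article does not say so.

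Which SD is meant, and how composites are scaled, may be settled in a fuller document that is not shown. The point does not rest on those details.

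**Conclusion.** The concern holds in a limited form. The rule as written has no retest-error, practice or regression-to-the-mean term, the same battery is repeated, and there is no untreated comparison, so the claim that it ensures functional significance is unsupported. The rule can mislabel a material share of unchanged participants: between 1.4% and 20.4% per domain over the assumed range, and between 7% and 60% of those at or below the 5th percentile at baseline. Highly reliable composites sit at the low end; domains with lower reliability or a practice gain sit higher. All these rates assume normal scores with SD 1 and a cohort at the normative mean. The consequence is confined to the supplementary statement of clinical relevance, so this is a change that should be made rather than a flaw in the primary test.

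**What to change.** - Define reliable change as (12-month score − score predicted from baseline)/standard error of prediction, with ±1.645 as the limits. Take the prediction equation from published or battery retest data. This allows for practice and regression to the mean as far as the reference matches the cohort and the retest interval.
- Use participants without PAP as the reference only in a sensitivity analysis. Section 2.2 says treatment follows clinical indication, the Discussion concedes confounding by indication, and the size of that group is not stated.
- Count a percentile shift only when the reliable-change criterion is also met.
- Standardise each domain composite to SD 1 in one reference population, used at both visits.
- Report reliable decline beside reliable improvement, by adherence. Noise produces both: without practice, limb 1 and its mirror image have the same false rate.
- Delete the sentence claiming that the rule ensures functional significance, or soften it.

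Under the reference model the false-improvement rate becomes 5% per domain at every baseline level, in place of a rate that varies with reliability, practice and baseline score.

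The cost is wording in the analysis plan, plus naming a retest reference. Over most of the assumed range fewer participants will be called improved. The exception is a very reliable composite: with SD 1 the limit is 1.645 × √(1−r²), which is 0.72 SD at r = 0.9. Without practice that is looser than the 1 SD limb across the whole cohort (5% against 1.4%), though still stricter for the baseline-impaired (5% against 7%).

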#### 2.5.2. Secondary Outcome Measures

##### Changes in Baseline Measures

After 12 months of PAP treatment, patients will undergo the same assessments as during their initial hospitalization (besides ApoE genotyping), following the original protocol. This will include overnight PSG, neuropsychological testing, brain imaging, brain volumetry, anthropometric measurements, blood and saliva samples, gut microbiome, vascular functions and baroreflex sensitivity assessments. All collected data will be compared with baseline values, allowing us to explore the associations between PAP therapy and changes in cognitive and other selected parameters. All secondary analyses are considered exploratory and hypothesis-generating.

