### 2.2. Study Design and Setting

This study employs a prospective, observational, longitudinal cohort design, conducted at the Sleep Laboratory of the 1st Department of Neurology, Faculty of Medicine, Comenius University, University Hospital Bratislava, Slovakia. The study will enroll at least 100 eligible participants with newly diagnosed mild to severe OSA, who have no history of chronic diseases (except for overweight and obesity) and are not receiving any chronic medication. The Sleep Laboratory has active research programs on sleep disorders, an established infrastructure for clinical studies, and a high volume of patient referrals. Participants meeting all inclusion criteria will receive detailed information about the purpose and procedures of the study before enrollment.

Diagnosis of OSA must first be confirmed by overnight PSG. Participants will then enter the cohort after meeting the inclusion/exclusion criteria described below. Trained research personnel will obtain informed consent from the patient after providing all the necessary information. Cognitive function, OSA-related measures (PSG variables), sleep parameters, brain magnetic resonance imaging (MRI) and volumetric measures, anthropometric parameters, blood and saliva biomarkers, gut microbiota composition, endothelial function, and baroreflex sensitivity will be assessed at baseline and after 12 months, together with neurological, pulmonary, and ear, nose, and throat (ENT) examinations. Those patients who are routinely clinically indicated for PAP therapy will receive treatment, and their adherence will be monitored throughout the study. PAP therapy is prescribed exclusively based on routine clinical indications and follows standard-of-care pathways. The study protocol does not mandate initiation, modification, or discontinuation of PAP therapy and does not include any study-driven therapeutic decision-making. Participants are not randomized to treatment groups, and no experimental group allocation is performed. Blinding of participants and investigators to PAP therapy status is not feasible due to the nature of the study design. Participants are invited to contact the principal investigator at any time to inquire about results. The general study timeline is described in Table 1.

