#### 2.5.3. Exposure Variables of Interest

##### PAP Therapy and Adherence to Treatment

The gold standard treatment of moderate/severe OSA is positive airway pressure (PAP) therapy, which works by holding the airway open using a pneumatic splint. There is evidence to suggest that compliant PAP therapy use can have beneficial effects on some of the consequences of this disorder. Adherence to the treatment will be measured through an adherence tracking system using smart memory cards, which will report all needed parameters. Adherence will be primarily analyzed as a continuous variable (e.g., average hours of use per night) to capture potential dose–response relationships with cognitive outcomes. In addition, secondary analyses will examine adherence as a categorical variable using standard criteria to classify participants as adherent or non-adherent (e.g., ≥4 h of use per night [23]), allowing for clinically interpretable group comparisons. To promote participant retention and complete follow-up, study assessments are scheduled in alignment with routine clinical visits where feasible.

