### 2.7. Data Analysis Plan

Descriptive statistics will be used to summarize demographic and clinical characteristics. The normality of continuous variables will be assessed using visual inspection (Q–Q plots, histograms) and statistical tests (e.g., Shapiro–Wilk). Continuous variables will be presented as mean ± SD for normally distributed data or median with interquartile range for non-normally distributed data. Categorical variables will be expressed as frequencies and percentages.

Primary analyses will evaluate within-subject changes in cognitive function over the 12-month period (i.e., change scores ΔT12–T0). These changes will be analyzed using linear mixed-effects models with a random intercept, which allow for repeated measurements and account for inter-individual variability. Fixed effects will include time, PAP adherence, and covariates such as age, sex, and education. An interaction term between time and adherence will be used to assess whether longitudinal changes differ according to adherence level.

Secondary analyses will explore associations between changes in cognitive outcomes and other measured variables, including sleep parameters, volumetric measures, anthropometric and metabolic indicators, biomarkers, and other selected laboratory measures (e.g., pNfL, ApoE genotype, gut microbiome composition), as well as indices of vascular health and autonomic nervous system function. These associations will be examined using Pearson or Spearman correlations between change scores (ΔT12–T0) and multiple linear regression models with a limited number of predictors (maximum of 4 per model) to minimize the risk of overfitting.

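### In the exploratory analyses, the raw 12-month change in respiratory polysomnography indices is a poor variable for relating PAP to cognition, whether the follow-up night is recorded off or on PAP

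*Protocol article*

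**What the plan says.** All places are in the protocol article.

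- **Baseline night.** Section 2.3.2 excludes "Prior therapy for OSA (e.g., PAP, upper airway surgery, oral appliance"), so the diagnostic PSG is an untreated recording.
- **Follow-up night.** Section 2.5.2 states that after a year of PAP "patients will undergo the same assessments as during their initial hospitalization (besides ApoE genotyping), following the original protocol". It adds: "This will include overnight PSG, neuropsychological testing, brain imaging, brain volumetry", among other measures.
- **Use of the repeat.** The same section says: "All collected data will be compared with baseline values, allowing us to explore the associations between PAP therapy and changes in cognitive and other selected" measures. Section 2.1 also plans to relate PAP adherence to change in the cognitive and physiological outcomes, and PSG-derived parameters head its list of OSA-related measures.
- **Analysis.** Section 2.7 names sleep parameters among the secondary variables: "These associations will be examined using Pearson or Spearman correlations between change scores (ΔT12–T0") and by multiple regressions with at most four predictors.
- **How PAP acts.** Section 2.5.3 describes PAP as a treatment "which works by holding the airway open using a pneumatic splint". Its effect on breathing, as described, is mechanical.
- **Who is treated.** Section 2.2: "Those patients who are routinely clinically indicated for PAP therapy will receive treatment". The cohort runs from mild to severe OSA, and Table 1 marks adherence as applicable only to some.

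Sections 2.5.2 and 2.7 do not say whether the 12-month night is recorded on or off PAP. Sections 2.5.2 and 2.7 (with the text that follows it) call the secondary analyses exploratory.

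**The concern.** A change score is useful here only if it carries the change in breathing that cognition could respond to, which is the change accumulated over a year of variable PAP use. One follow-up night can be recorded in two ways, and neither gives that quantity for respiratory indices.

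- **Off PAP.** The splint is absent, so the difference from baseline reflects the underlying disease (weight, for example) and night-to-night variation. A null association with PAP use or with cognition would say little about treatment.
- **On PAP.** Residual AHI lies near a floor for almost everyone, so follow-up minus baseline is nearly minus baseline. An association of this change with cognitive change would be an association of baseline severity with cognitive change, and could be reported as a treatment response.

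If users are recorded on PAP and the others untreated, one pooled correlation combines the two quantities.

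**Working it through.** **Inputs.** From the protocol: untreated baseline, AHI at least 5/h, one repeat night, change-score correlations, PAP acting as a splint. The protocol gives no AHI spread, residual AHI, night-to-night variation or hours of use on which to base a calculation. Those values are assumptions below, shown as ranges. The plan has no figure of its own on this point. Its sample-size figures reproduce and do not change: 34 pairs give power 0.808 and 34/0.85 = 40; 85 participants with f² = 0.15 and four predictors give 0.803 and 85/0.85 = 100.

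**1. One patient.** Assume untreated AHI 30/h, residual AHI 4/h on PAP and 6.5 h of sleep. Year-average change = −(hours/6.5) × (30 − 4).

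| Use, h/night | Year-average change | On-PAP night | Off-PAP night |
|---|---|---|---|
| 1 | −4 | −26 | about 0 |
| 3 | −12 | −26 | about 0 |
| 5 | −20 | −26 | about 0 |
| 6.5 | −26 | −26 | about 0 |

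Neither single-night column varies with use.

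**2. Off-PAP night.** Simulated with no carry-over of PAP's effect. The year's true mean change was about −15 to −20/h, and the measured mean change was about +1/h. The measured change correlated about −0.05 with the true change and about 0 with use. A second simulation (median AHI 18–25/h, night-to-night SD 5–12/h, residual about 4/h, about 4.5 of 6.5 h use) gave −0.02 to 0.00 with the true change.

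**3. On-PAP night.** Let B be baseline AHI and R residual AHI, with SDs SDb and SDr and correlation ρ. Then

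corr(R − B, B) = (ρ·SDr − SDb) / √(SDb² + SDr² − 2ρ·SDb·SDr).

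- SDb 25, SDr 2, ρ 0: −25/√629 = −0.997.
- SDb 20, SDr 4, ρ 0.3: −18.8/√368 = −0.98.
- SDb 10, SDr 6, ρ 0.5: −7/√76 = −0.80.
- Weakest case tried, SDb = SDr = 10, ρ 0.5: −5/√100 = −0.50.

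In simulation the on-PAP change correlated about 0.00 with use. Its correlation with the year's true change was 0.71 to 0.89 in most runs, and 0.56 among treated patients when 40% stopped PAP but were still recorded on it. Most of this comes from baseline severity, which both quantities contain: given baseline AHI, the partial correlation is only about 0.1 to 0.2.

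**4. Mixed cohort.** Assumed: log-normal baseline AHI (median 25, log SD 0.7), treatment from 15/h in the simulation only, residual mean 5 and SD 4, and stoppers and untreated participants recorded off PAP. With 0, 20 and 40% stopping, whole-cohort corr(change, baseline) is −0.99, −0.80 and −0.63. Among those recorded on PAP it stays −0.99. The pooled score then also encodes who was on treatment.

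**5. Other PSG parameters.** Where the SD is the same at both visits, as may hold for sleep-stage shares, R² of change with baseline is (1 − ρ)/2. That is 0.40 at ρ = 0.2 and 0.10 at ρ = 0.8, so the near-restatement of baseline is not shown for them.

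**6. Usage-weighted AHI.** Let f be the fraction of sleep on PAP. The weighted change is f·R + (1 − f)·B − B = −f·(B − R). It also contains B, and correlates about −0.81 to −0.87 with baseline. Given baseline, its partial correlation with the year's true change is about 0.8 to 0.9. Part of that is by construction, because the simulated truth uses the same formula.

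**The case against.** The strongest reply has four parts.

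- **The recording condition is operational detail** that a condensed article may leave to the full protocol. This stands: its absence alone is not an error. The point rests on what the text does fix, namely the repeat, the change score and its use for PAP and cognition. The score has a defect under either condition.
- **The protocol never says that PSG change measures a year of treated breathing.** Adherence by memory card is the declared exposure, and section 2.4.1 uses PSG to characterize severity. This stands in part: an off-PAP repeat validly describes change in underlying disease. But sections 2.1 and 2.5.2 also use the change to explore associations with PAP.
- **The analysis is not limited to crude correlations.** Section 2.7 allows small regressions, and the Discussion plans adherence-stratified and covariate-adjusted analyses. This stands in part: pooling is possible rather than stated. Neither place commits to baseline AHI as a covariate or to separating recording conditions.
- **The figures rest on assumed inputs.** They do, and drawing use independently of severity helps produce the zero correlation with hours. The direction follows from the splint mechanism and the residual floor.

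A reader might infer that all PSG change scores are unusable, that the primary result is compromised, or that usage-weighted AHI should replace the PSG change. The documents support none of these. The argument covers respiratory indices only. The primary model uses adherence, not PSG change. The weighted index shares the dependence on baseline and needs residual AHI and home sleep time, which the protocol does not confirm are recorded.

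**Conclusion.** The concern holds for respiratory PSG indices (AHI, desaturation) in the exploratory analyses. Off PAP, their raw 12-month change is essentially unrelated to the year's reduction (about −0.06 to 0.00 in the simulations). Among users recorded on PAP, it correlates −0.80 to −0.997 with baseline AHI over the main assumed range (−0.50 in the weakest case tried) and about 0 with hours of use. These sizes assume no carry-over of PAP's effect, a low residual AHI, and use unrelated to severity. In a mixed cohort the correlation with baseline weakens to between −0.80 and −0.63 when 20 to 40% stop, because the score then also encodes treatment status. The consequence is possible misreading of secondary associations. The primary time-by-adherence analysis and the sample size are untouched.

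**What to change.** Amend sections 2.5.2 and 2.7, and reconcile them with section 2.5.3:

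1. Record for every follow-up PSG whether it was made on or off PAP.
2. Analyse respiratory change scores only within one recording condition, and do not pool the two.
3. Interpret off-PAP change as change in underlying disease.
4. For respiratory indices, replace simple change-score correlations by regressions that include baseline AHI.
5. If the memory cards report residual AHI (to be confirmed, since section 2.5.3 does not name it), add the usage-weighted AHI change as a supplementary treatment-related variable. Adjust it for baseline AHI too, and give a sensitivity range for home sleep time.

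The cost is one of the four predictor slots, smaller strata, and an assumed sleep time for the supplementary variable. Device-scored residual AHI is also not identical to PSG-scored AHI. Enrolment is ongoing, so the wording can be settled before analysis. The PSG procedure and clinical management stay as they are.
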